### Study design

In this randomised controlled trial, participants are randomised centrally into a 1:1 ratio for treatment with online HDF or treatment with low-flux HD. Randomisation is stratified by the participating centres and occurs in blocks. The follow-up period is three years. At present, 24 dialysis centres have agreed to recruit the required number of patients. The study is conducted according to good clinical practice (GCP) guidelines.

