### Data collection

#### Baseline and follow-up data registration

At baseline, all relevant information will be documented: i.e. demographical data, information on cardiovascular risk factors, time on dialysis, cause of renal insufficiency, and medication. A follow-up visit will be scheduled every three months. During this visit, the occurrence of CV events, death, and hospitalisation will be documented. In addition, blood pressure, body weight and the achieved filtration and substitution dose per treatment will be registered. Case record forms are provided using the TeleForm system (version 8.1.1, Cardiff Software Inc, Vista, CA, USA). As all completed forms are scanned, no data entry by typing is needed. Registration of all data will be performed in each centre by the attending nephrologists and research nurses.

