#### Primary outcome

The primary outcome variable is the time until the occurrence of an event defined as 'all cause mortality'. Results will be presented as Kaplan-Meier curves for the two treatment arms and the difference between the two treatments will be analysed using a log-rank test. The log-rank test will be adjusted for the effect of cumulative data analyses (see below).

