#### Sample size considerations

The sample size of the present study is based on the following event rates: the 3-year all cause mortality rate among subjects with ESRD is 44% based on data from the Dutch renal replacement registry (RENINE) [38]. CV mortality constitutes 40–60% of the total group of deaths, leading to a 3 year CV mortality rate of 22% in HD patients. Assuming that the incidence of non-fatal CVD is equal to the CV mortality rate (22%), the three-year incidence of fatal and non-fatal CVD is 44%. In addition, based on experience ± 8% of the ESRD patients will undergo renal transplantation yearly and as such is being censored in the trial.

Assuming that HDF will reduce all cause mortality with 20%, it has been estimated that with a two-sided alpha of 0.05 and a power of 80%, about 772 patients need to be enrolled and followed for three years. In these patients about 250 events are expected to come to a decision. Note that the total number of patients to be included cannot be specified in advance because of the planned sequential interim analyses, as described below.

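### Efficiency improvement: the primary mortality test and its sequential Z and V use none of the baseline prognostic data collected, so available power goes unused

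*Protocol article*

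**What the plan says.** Under Primary outcome, the endpoint is time to death from any cause and "the difference between the two treatments will be analysed using a log-rank test". The section continues: "The log-rank test will be adjusted for the effect of cumulative data analyses". That adjustment concerns multiplicity over looks; no covariate or stratum is named.

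Interim analysis carries the same statistic into the stopping rule. Z is observed minus expected control-arm events under equivalence, and V is about a quarter of the events. The treatment measure θ is minus the log hazard ratio, obtained from overall survival of 0.648 on HDF and 0.56 on HD.

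Baseline and follow-up data registration says that "demographical data, information on cardiovascular risk factors, time on dialysis, cause of renal insufficiency, and medication" are documented at baseline. Study design says: "Randomisation is stratified by the participating centres and occurs in blocks". Under Secondary outcomes, by contrast, clinical centre is an independent variable in the carotid intima-media thickness model.

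**The concern.** The trial has no upper age limit and enrols both incident and prevalent dialysis patients, so the risk of death is likely to vary widely within each arm. Randomisation balances centre only; age, diabetes and time on dialysis are left to chance. When such factors predict death, an unadjusted log-rank test extracts less from the same deaths than a test that conditions on them.

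This matters because deaths are the scarce resource. The sequential rule may have to run well beyond the expected number of events, so a sharper test could bring an earlier decision or a better chance of detecting a real effect, with no extra patient or measurement.

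**Working it through.** **Inputs from the article.** Survival at three years 0.56 (HD) and 0.648 (HDF); two-sided alpha 0.05; power 80%; double triangular test; V = events/4; 772 patients; about 250 events; about 8% per year censored at transplantation.

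**Input not in the article.** How strongly the baseline factors predict death. It is expressed as the SD of the log-hazard score captured by the covariates, with an assumed range of 0.3 to 1.0 (C-statistic about 0.59 to 0.74).

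**Step 1: reproduce the plan.**

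- θ = −ln(ln 0.648 / ln 0.56) = −ln(0.7483) = 0.290, as stated.
- Boundaries, with 0.025 per side: θ* = θ × 2 × 1.96 / (1.96 + 0.8416) = 0.4057; a = 2 ln(20) / θ* = 14.77; c = θ*/4 = 0.1014. The outer boundary is Z = a + cV and the inner one Z = −a + 3cV, mirrored for the other side.
- They meet at V = a/c = 145.6, which is 4 × 145.6 = about 582 events at most.
- In 100,000 simulated paths with a correction for discrete looks, power is 0.80, two-sided alpha is about 0.05, and mean events are 253 to 257 under the alternative, depending on look spacing. The stated figure of about 250 is reproduced within 3%.

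**Step 2: the effect once prognosis is conditioned on.** Exponential hazards were solved so that overall survival stays at 0.56 and 0.648 for each assumed SD. The conditional hazard ratios that result are in the table. They lie further from 1 than the marginal 0.748.

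**Step 3: planned boundaries with the conditional effect.** The boundaries of Step 1 are unchanged, θ is minus the log of the conditional hazard ratio, and V is assumed to stay near events/4.

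| SD captured | C (approx.) | Conditional HR | Sequential power | Mean events |
|---|---|---|---|---|
| none (plan as written) | – | 0.748 | 0.80 | 253 |
| 0.3 | 0.59 | 0.743 | 0.82 | 251 |
| 0.5 | 0.64 | 0.734 | 0.85 | 245 |
| 0.7 | 0.67 | 0.720 | 0.89 | 234 |
| 1.0 | 0.74 | 0.693 | 0.95 | 212 |

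**Step 4: cross-check on full patient-level data.** Here 772 patients were simulated for three years with 8% per year censoring and one fixed analysis, 1,500 runs per setting (Monte Carlo error about 1 point).

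- Expected deaths: with γ = 0.08 and λ = −ln(S)/3, the probability of an observed death is λ/(λ+γ) × (1 − exp(−3(λ+γ))). This is 0.396 on HD and 0.316 on HDF, mean 0.3557, so 772 × 0.3557 = about 275.
- Power, log-rank against adjusted: 0.67 v 0.69 (SD 0.3), 0.67 v 0.71 (0.5), 0.68 v 0.76 (0.7), 0.68 v 0.86 (1.0).
- Type I error with no treatment effect and SD 1.0: 0.053 unadjusted, 0.050 adjusted.

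The fixed-analysis levels do not describe the planned trial. They confirm that adjustment gains power at these strengths while type I error stays near 5%.

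**The case against.** The strongest reply is that nothing is stated wrongly. The log-rank test is valid, it addresses the marginal contrast on which the trial was sized, and it meets its own 80% target. Covariate lists are often left to an analysis plan, and none is shown here. The first two statements stand, and they are why this is an efficiency point and not a defect. The third stands only in part: the article itself names the primary test and defines Z and V, so an adjusted analysis elsewhere would not change the statistic that drives stopping.

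Four stronger readings are tempting and not supported.

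- *Without covariates the trial has only about 68% power.* That level belongs to a single fixed analysis at about 275 deaths. The plan is sequential, says the total number of patients cannot be fixed in advance, and reaches 80%.
- *The baseline factors are strong predictors.* The article does not say so. With weak factors (SD 0.3) the gain is about 2 points. The simulation also uses a perfectly measured score, so a short list may capture less than the full score would.
- *Adjustment costs nothing.* It changes θ to a conditional quantity and needs complete baseline data at every two-monthly look.
- *The unadjusted result is biased by omitted covariates or chance imbalance.* The marginal and conditional hazard ratios are different quantities, and randomisation with the test's type I error already allows for chance imbalance.

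Two practical objections also stand. More than 150 patients had been included by April 2005 and the monitoring board sees unblinded data, so the covariates must be chosen without reference to outcomes by arm. Early looks will have few deaths, which limits how many covariates the model can carry.

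**Conclusion.** The point holds as a recommended efficiency improvement. The primary test and the sequential Z and V leave out baseline prognosis and the centre strata, although both are at hand. The gain over the planned 80% is about 2, 5, 9 or 15 points of power (82%, 85%, 89% or 95%), with about 2, 8, 19 or 41 fewer deaths on average (253 less 251, 245, 234 or 212), for a captured SD of 0.3, 0.5, 0.7 or 1.0.

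These figures rest on the assumed prognostic strength, on proportional hazards given the covariates, and on V staying near events/4. They do not include any effect of stratifying by centre, which was not sized. The direction of the gain is secure if the covariates predict death; its size is not known from the article.

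**What to change.** In Primary outcome and Interim analysis:

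1. Name a short list of baseline covariates, for example age, diabetes, prior cardiovascular disease and time on dialysis, with a simple rule for missing values. Fix both without reference to unblinded outcome data.
2. Define Z and V as the score and information for treatment from a Cox model with those covariates, keeping the present sign convention. Use them at every look and at the final analysis, with the (Z,V) boundaries unchanged.
3. State that θ is then a log hazard ratio conditional on the covariates, and that the survival figures of 0.648 and 0.56 remain the marginal basis of the sample size.
4. State whether centre enters as a stratum, given that many centres will have few or no deaths at early looks.
5. Keep the unadjusted log-rank test and the Kaplan-Meier curves as supportive.

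The cost is wording and some programming for the monitoring board's biostatistician. Baseline forms must be complete before each look, the list must suit the few deaths at early looks, and the reported hazard ratio becomes conditional. No extra patients, visits or measurements are needed.

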#### Secondary outcomes

CV events are considered as secondary outcome variables. They will be analysed and presented as described for the primary outcome variable.

The primary analysis of CIMT progression will employ a linear random coefficient (Laird-Ware) model using real visit days, treatment and clinical center as independent variables. for each participant, the intercept and slope of CIMT change over time is assumed to be a normally distributed random variable with different means for the two treatment groups. The mean slope for the HDF treatment group will be compared to that for the low flux group using linear contrasts and a 5% significance level. Additional exploratory analyses will evaluate the impact of including baseline CIMT, lumen diameter, and ultrasound reader as additional co-variates.

The data analytic approach to arrive at the PWV outcome variable and the LVMi outcome variable is similar to that of the CIMT outcome. Adjustments that will be taken into account in the estimates are changes in MAP and changes in heart rate, since both are closely related to PWV.

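### The CIMT, PWV and LVMi slope models, as written, let the mean slope depend on treatment only, so a slope test after centre-stratified randomisation may report too wide a standard error

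*Protocol article*

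**What the plan says.** The protocol article (Methods, Statistical methods, Secondary outcomes) describes the main CIMT analysis as a "linear random coefficient (Laird-Ware) model using real visit days, treatment and clinical center as independent variables". Each participant's intercept and slope is "assumed to be a normally distributed random variable with different means for the two treatment groups". The hypothesis is about slopes: "The mean slope for the HDF treatment group will be compared to that for the low flux group using linear contrasts", at a 5% significance level.

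PWV and LVMi follow the same route: "The data analytic approach to arrive at the PWV outcome variable and the LVMi outcome variable is similar to that of the CIMT outcome". The exploratory CIMT analyses consider "including baseline CIMT, lumen diameter, and ultrasound reader as additional co-variates". No centre-by-time term is named in the main or the exploratory analyses, and none is ruled out.

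Under Study design, allocation is 1:1 and "Randomisation is stratified by the participating centres and occurs in blocks". The article counts 24 centres in the trial. Under Vessel wall measurements it says that only a limited number of them, not specified, will measure CIMT and PWV.

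**The concern.** A factor used to stratify randomisation should normally appear in the analysis in a form that acts on the quantity being tested. Here that quantity is a difference in slopes. A centre term that only shifts the level of the measurement absorbs differences between centres at baseline, but not differences in how the measurement changes over time. Those could come from local acquisition technique, equipment, or case mix that affects progression.

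Because the arms are balanced within centre, such differences largely drop out of the treatment contrast. A model with one common slope per arm does not know this. It counts the variation between centres as variation between patients and carries it into the standard error. The reported interval is then wider than the estimate deserves and the test rejects less often than 5% under the null. At stake is some power in sub-studies that already rest on a subset of centres. The estimate is not biased and false positives do not increase.

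**Working it through.** **Inputs from the protocol article.** 1:1 allocation, stratified by centre in blocks (Study design). Test of the difference in mean slope at 5% (Secondary outcomes); the side is not stated for this test and two-sided is assumed. 24 centres in the trial; the number measuring CIMT or PWV is not given. No sample size, standard deviation, effect size or power is given for CIMT, PWV or LVMi, so there is no stated figure to reproduce.

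**Assumed inputs.** Let ρ be the share of the variance of patients' estimated slopes that lies between centres. It is not in the documents; a range from 0 to 0.30 is used. The effect is set to 2.8 standard errors, which gives 80% power when ρ = 0.

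**Closed form.** Scale the standard error (SE) at ρ = 0 to 1. With balance within centre and complete visits:

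- True SE of the contrast: √(1 − ρ).
- SE reported without centre-by-time: about 1, so reported/true = 1/√(1 − ρ).
- Test size without the term: 2Φ(−1.96/√(1 − ρ)).
- Power without the term: Φ((2.8 − 1.96)/√(1 − ρ)).
- Power with the term: Φ(2.8/√(1 − ρ) − 1.96).

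| ρ (assumed) | reported/true SE | size without | power without | power with | difference (points) |
|---|---|---|---|---|---|
| 0 | 1.000 | 0.050 | 0.800 | 0.800 | 0 |
| 0.02 | 1.010 | 0.048 | 0.802 | 0.807 | 0.6 |
| 0.05 | 1.026 | 0.044 | 0.806 | 0.819 | 1.4 |
| 0.10 | 1.054 | 0.039 | 0.812 | 0.839 | 2.7 |
| 0.20 | 1.118 | 0.028 | 0.826 | 0.879 | 5.3 |
| 0.30 | 1.195 | 0.019 | 0.842 | 0.917 | 7.5 |

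**Simulation.** Patient slopes with permuted blocks of 4 within centre, 4,000 runs for test size and 2,000 for power. Three assumed layouts: 200 patients in 5 centres, 400 in 10, 768 in 24. Ranges are over the three layouts.

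| ρ | reported/true SE | size without | power without | power with |
|---|---|---|---|---|
| 0 | 0.997–1.009 | 0.046–0.051 | 0.796–0.798 | 0.795–0.797 |
| 0.05 | 1.033–1.042 | 0.040–0.043 | 0.792–0.812 | 0.808–0.822 |
| 0.10 | 1.039–1.057 | 0.037–0.043 | 0.798–0.818 | 0.830–0.838 |
| 0.20 | 1.093–1.124 | 0.026–0.035 | 0.802–0.843 | 0.861–0.886 |
| 0.30 | 1.157–1.197 | 0.018–0.025 | 0.840–0.858 | 0.915–0.925 |

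With the term, test size stayed between 0.043 and 0.056. The simulation agrees with the closed form within simulation error, apart from somewhat lower SE ratios in the layouts with few centres at the larger shares.

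**What stratification still delivers.** With 768 patients in 24 centres the true SE of the contrast fell from 0.0715 at ρ = 0 to 0.0640 at ρ = 0.20, a ratio of 0.895 against √0.8 = 0.894. It was the same with or without the centre-by-time term. Only the reported SE differs.

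**Does centre in the level help a slope test?** Twelve mixed-model fits with random intercept and slope (8 centres, 192 patients, 25% early dropout) gave a mean reported SE for the slope contrast of 0.1488 with no centre term, 0.1488 with centre in the level, and 0.1408 with centre in level and slope. Twelve fits show the mechanism; they are too few to size it.

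**The case against.** The strongest objection is that the article lists variables, not model terms. Treatment stands in the same bare list, yet plainly acts on the slope, so centre might be meant to do so too. Interaction terms are the kind of detail that a condensed article leaves to the full protocol or analysis plan. This stands in part: a centre-by-time term is not excluded, and a reader should not conclude that the sponsor has rejected one. But the article goes on to say what shifts the mean intercept and slope, and names treatment alone. Centre in the level only is the plain reading of what is written.

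A reader might also infer that stratifying by centre gains nothing for these comparisons. The documents do not support that. Balance within centre removes centre drift from the contrast and lowers its true variance; the loss is confined to the reported standard error and the test built on it.

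The size rests on an assumed share. For CIMT the article provides a uniform protocol, centre training, sonographer certification, core-laboratory reading and quality control; for PWV, central training and regular data checks; for LVMi, a uniform protocol and core-laboratory analysis. These measures do not show that the share is zero, since central reading cannot undo local differences in acquisition, but they make the smaller shares more plausible.

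Finally, one might want ultrasound reader moved from the exploratory to the main CIMT model. Scans are read in a core laboratory, so reader is not an attribute of the centre. The stratification argument does not reach it and no calculation here supports the move.

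**Conclusion.** The point holds as a minor one. On its plain reading, the specified slope model does not use the stratification factor where the hypothesis lies. If centres differ in slope, the reported standard error is too wide and the test is conservative: about 3%, 5% and 12% at assumed between-centre shares of 5%, 10% and 20%, with power about 1, 3 and 5 points below what the same data could give. At a share of 0 nothing is lost, and at 2% the loss is about half a point.

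These figures assume a two-sided test, balance within centre, complete visits and 80% power without centre variation. The consequence is lost precision on secondary outcomes. The mortality comparison is not touched.

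**What to change.** State in the analysis plan, before unblinding, that the CIMT, PWV and LVMi slope models contain a centre-by-time term in addition to centre and treatment-by-time, and give a rule for pooling very small centres. If such a term was always intended, one sentence saying so settles the matter. Ultrasound reader can stay as the planned exploratory covariate.

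The cost is one degree of freedom per centre (after pooling) less one, and no new data. In the simulations power was unchanged to within 0.001 when centres did not differ in slope.

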#### Sample size considerations

The sample size of the present study is based on the following event rates: the 3-year all cause mortality rate among subjects with ESRD is 44% based on data from the Dutch renal replacement registry (RENINE) [38]. CV mortality constitutes 40–60% of the total group of deaths, leading to a 3 year CV mortality rate of 22% in HD patients. Assuming that the incidence of non-fatal CVD is equal to the CV mortality rate (22%), the three-year incidence of fatal and non-fatal CVD is 44%. In addition, based on experience ± 8% of the ESRD patients will undergo renal transplantation yearly and as such is being censored in the trial.

Assuming that HDF will reduce all cause mortality with 20%, it has been estimated that with a two-sided alpha of 0.05 and a power of 80%, about 772 patients need to be enrolled and followed for three years. In these patients about 250 events are expected to come to a decision. Note that the total number of patients to be included cannot be specified in advance because of the planned sequential interim analyses, as described below.

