**Figure 2 F2:**
[figure not shown]
**Sequential analysis**. Boundaries for a double sequential triangular test with α = 0.05, power 0.80 and hazard ratio 0.75. Z is the observed number of events in the control group minus the expected number of events given treatment equivalence. V is approximately equal to a quarter of the number of events observed.

1) the upper or the lower (continuous) boundary is crossed: stop the data collection and reject the null hypothesis;

2) one of the inner wedge-shaped (dashed) boundaries is crossed: stop the data collection and accept the null hypothesis;

3) continue the data collection: the cumulative data are inadequate to draw a conclusion yet.

An independent Data Safety and Monitoring Board (DSMB) will evaluate the results of the sequential interim analyses. The DSMB consists of a biostatistician (chair), a nephrologist, an internist, and a clinical epidemiologist. The biostatistician will perform the sequential analyses. The executive committee will provide the DSMB every 2 months with the relevant database to perform the unblinded analyses. The main task of the DSMB is to decide whether the analyses provide enough evidence of either efficacy or no efficacy with respect to the primary outcome and formulates recommendations for the executive committee on the continuation of the trial. The DSMB may also offer unsolicited recommendations on the continuation of the trial, for example after publication of results of similar trials.

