## Conclusion

Online HDF is gaining popularity, as recent technical advances have made it possible to safely replace considerable amounts of fluid at reasonable cost. In addition, accumulating evidence indicates that the correction of the uremic state is improved by online HDF, if compared to standard HD. However, at present it is unclear whether long-term treatment with HDF ultimately results in an improved clinical outcome. Therefore, CONTRAST is initiated, a randomised controlled trial of sufficient sample size to detect differences in survival and cardiovascular events. Patients will be randomised between low-flux HD and online HDF and followed for 3 years. Over 20 Dutch dialysis centers participate in this study and approximately 800 incident and prevalent HD patients will be recruited. By April 2005, more than 150 patients were included.

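### 772 patients followed three years matches the average stopping point of the triangular test; 80% power holds only if data collection may run beyond that size

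*Protocol article*

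**What the plan says.** Under Sample size considerations the article gives a control rate, "the 3-year all cause mortality rate among subjects with ESRD is 44" percent, and an effect, "Assuming that HDF will reduce all cause mortality with 20" percent. It adds that about 8% of patients a year are transplanted and then censored. From these it concludes, "with a two-sided alpha of 0.05 and a power of 80" percent, that "about 772 patients need to be enrolled and followed for three years", and that "about 250 events are expected to come to a decision". The next sentence says that the total cannot be fixed beforehand, because the interim analyses are sequential.

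Under Interim analysis the hazard ratio is built from three-year survival of 0.648 on HDF and 0.56 on HD. The Figure 2 legend names the test: "Boundaries for a double sequential triangular test with α = 0.05, power 0.80 and hazard ratio 0.75". Information V is about a quarter of the events. The third listed decision is to go on collecting data while the evidence is inadequate.

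Elsewhere the size reads as settled. Study design says "The follow-up period is three years". The Abstract gives about 800 patients followed for three years. The Conclusion gives the same size and duration and calls the trial "a randomised controlled trial of sufficient sample size to detect differences in survival and cardiovascular events".

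**The concern.** A sequential test has no single event count that secures its power. It has an average stopping point, a long upper tail and a maximum. Its 80% power includes the trials that travel into that tail. If patients and follow-up are set to supply little more than the average, many of those trials run out of deaths before they reach a boundary.

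This concerns the primary endpoint. If HDF has the hypothesised effect, a trial that ends at the stated size could well close with neither a rejection nor an acceptance of the null hypothesis, although readers have been told that it has 80% power.

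**Working it through.** **Inputs.** From Sample size considerations: alpha 0.05 two-sided, power 80%, 44% control mortality at three years, 20% relative reduction (so 35.2% on HDF), 8% yearly transplantation, 772 patients, 250 events. From Interim analysis and Figure 2: survival 0.56 and 0.648, hazard ratio 0.75 (ln 0.648 / ln 0.56 = 0.748), V = events/4. From Study design: 1:1 allocation, three years. Figure 2 is not shown, so standard triangular boundaries are assumed.

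**1. Reproducing 250 events.** Combine two triangular tests, each with one-sided alpha 0.025 and power 0.80.
- θ = −ln 0.75 = 0.2877; rescaled, θ* = 2 × 1.960/(1.960 + 0.842) × 0.2877 = 0.4025.
- a = (2/θ*) × ln(1/0.05) = 14.88; c = θ*/4 = 0.1006.
- The outer boundary is Z = a + cV and the inner one Z = −a + 3cV. They meet at V = a/c = 147.9, about 592 events. The inner wedge opens at V = a/(3c) = 49.3, about 197 events.
- Simulated at hazard ratio 0.75 with looks every 8–12 events and a discrete-look correction: power about 0.80–0.81, two-sided alpha about 0.05, mean stop about 258–260 events, median 248–252, 90th percentile about 400.

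So 250 reproduces, as an average. About half of trials under the hypothesised effect need more.

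**2. Reproducing 772 patients.** 250/(0.352 × 0.92) = 772.0, that is, average events divided by HDF-arm mortality with a single 8% loss. The article does not state this route; it is inferred. A fixed two-sided comparison of 44% with 35.2% gives 968. A one-sided 0.05 version gives 762, which is close but contradicts the stated two-sided alpha.

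**3. Deaths in three years.** Without censoring: 386 × (0.44 + 0.352) = 306 from 772 patients, and 400 × 0.792 = 317 from 800. With transplantation, take exponential hazards h = −ln(0.56)/3 = 0.193 and −ln(0.648)/3 = 0.145, and k = −ln(0.92) = 0.083 a year. The probability of death, h/(h + k) × (1 − exp(−3(h + k))), is 0.394 on HD and 0.314 on HDF. That gives 386 × 0.708 = 273, or 400 × 0.708 = 283.

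**4. Power if data collection ends there (hazard ratio 0.75).** Single log-rank test: Φ(√D/2 × 0.2877 − 1.960). For D = 273 this is Φ(8.26 × 0.2877 − 1.960) = Φ(0.417) = 66%.

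| Patients | Deaths | Single log-rank test | Triangular test: efficacy | Triangular test: undecided |
|---|---|---|---|---|
| 772, with censoring | 273 | 66% | 49–51% | 41–43% |
| 800, with censoring | 283 | 68% | about 54% | 36–37% |
| 772, no censoring | 306 | 71% | 58–59% | about 31% |
| 800, no censoring | 317 | 73% | 61–62% | 26–27% |

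The undecided share depends on look timing. The 800-patient rows assume a look exactly at the last death; doing the same for 772 lowers those entries by one or two points. The single test is an upper bound, since repeated looks cannot add power at the same maximum information. For reference, a single test needs 4 × (1.960 + 0.842)²/0.2877² = 379 deaths for 80%.

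**The case against.** The article does not flatly cap the trial. The sentence after the 772 and 250 figures leaves the total open, and the third interim decision is to continue. Run to a boundary, the test has its stated power. That stands, and it makes the shortfall conditional. A reader might infer that the design simply fails to deliver 80% power; the documents do not support that.

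A reader might also set 273–306 deaths against 379 and call the difference the deficit. But 379 belongs to a single fixed test. The planned test has no one required count, and cut off at 379 deaths it would itself show efficacy in only about 70–72% of trials.

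Nor does the article claim that 250 events secure the power: its wording is an expectation, and the stated aim of the sequential design is to need fewer patients on average. 772 patients do supply more deaths than that average.

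Finally, the maximum may be legible in Figure 2 or in a fuller protocol, so its absence from the text is not charged as an error.

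What remains is the sentence itself, which attaches 80% power to 772 patients and three years, and the three other places that repeat the size and/or duration as settled. The stated rationale for sequential testing speaks only of needing fewer patients, so it gives no hint that more than 772–800 might be required.

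**Conclusion.** The point holds conditionally. The stated size corresponds to the average stopping point, and 80% power belongs to the test only when it may run to a boundary. If collection ends at 772–800 patients and three years, power at hazard ratio 0.75 is at most 66–73%. For the planned test it is about 49–62%, and at 772 patients 31–43% of trials are undecided. The open-ended sentences and the fixed size and follow-up contradict each other, and the power claim depends on which of them governs.

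The figures assume exponential survival, three full years of follow-up for every patient, no loss other than transplantation, and standard triangular boundaries.

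**What to change.** In Sample size considerations, describe 250 events and 772 patients as the expected size at stopping, not as the size that gives 80% power. State the boundary maximum (about 592 events on standard boundaries; the sponsor should insert the value from its own design software). State that 772–800 patients followed for three years give at most 66–73% power.

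Then reconcile the Abstract, Study design, Sample size considerations and Conclusion with the decision to continue. Either say that accrual or follow-up goes on until a boundary is crossed, or declare a cap and report the lower power.

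The rewording costs little beyond a less favourable power figure under a cap. Continuing has a real cost: about one trial in ten under the hypothesised effect would need some 400 events, which at three years each is 400/0.396 = 1,010 patients without censoring or 400/0.354 = 1,130 with it, unless follow-up is lengthened instead.

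Following everyone's vital status to one common closing date, three years after the last randomisation, is an optional partial gain without extra patients. Accrual time is not given; assuming 2–4 years, it yields about 325–362 deaths with transplant censoring. At 345 deaths (three-year accrual) the triangular test has about 65–67% power and a single test 76%. It costs longer follow-up of early entrants and does not restore 80%.
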